## **1. BACKGROUND**

According to data from the National Institute of Statistics, Spain continues to experience an aging process. Currently, 18.4% of the population is over 65 years old, and the population segment that is growing the most is the group of individuals over 80 years old, which currently represents 6% of the total population and is expected to increase to 9% in the next 15 years (1). One of the factors that most influence successful and healthy aging is functional independence, understood as the ability to independently perform activities of daily living (ADL) (2).

Disability associated with hospitalization (DAH): Hospitalization often impairs the functional capacity of elderly individuals, especially the frailest ones (3-6). This DAH is due to multiple barriers to mobility during hospitalization related to the patient (disease, comorbidities, etc.), treatment (rest, procedures, medications, etc.), the institution (availability of personnel, assistive equipment, etc.), and the attitudes of the patient and staff (7). A recent study demonstrates that beyond individual risk factors, one of the main factors associated with DAH at discharge and 1 month later is low mobility during hospitalization (5). Ten days of bed rest cause a significant loss of total lean mass and strength in the lower limbs (8, 9). Muscle strength loss can be as high as 5% per day, so ten days of hospitalization can lead to a 50% loss of strength (5). Furthermore, the consequences of inactivity are more severe in the elderly compared to younger individuals (10). DAH is highly prevalent: between 40-50% of hospitalized elderly individuals, even for a short period of time, experience a decline in their functional capacity at the time of discharge (11-14). The progression of this decline once the acute illness that led to hospitalization has resolved is highly variable: between 30 and 60% of elderly individuals who experienced disability during the hospitalization recover it some time after discharge (15). Data collected in our acute care unit show that 389 out of 627 patients (62%) are discharged with DAH (data being prepared for publication). The consequences of disability are devastating for the patient and the healthcare system (5). Many patients who are discharged with new disabilities and do not recover are unable to live alone, requiring supervision at home or institutionalization into a residential facility. Additionally, DAH is associated with poor hospital outcomes: longer stays, increased complications, and increased mortality. Thus, elderly individuals who experience less functional deterioration during hospitalization have a 10.7% three-month mortality rate, compared to 36.7% for those who experience the greatest functional deterioration (16). Data from our service indicate an increase in mortality at 6 and 12 months for patients discharged with DAH, compared to patients who did not experience deterioration or recovered their functional status at discharge (data being prepared for publication). Typically, hospital stays do not promote mobility in the elderly. Between 73 and 83% of the time an elderly individual is hospitalized, they are usually bedridden (17, 18). Even very short hospital stays can involve bed rest and low levels of activity, which are associated with negative functional outcomes (6). Compared to patients with higher levels of activity during hospitalization, those with bed rest or low levels of any type of activity (physical therapy, independent or assisted activity) had higher rates of DAH and a greater risk of institutionalization and death at discharge and thirty days post-discharge (6, 19). This relationship between low mobility levels and functional decline remains significant after adjusting for multiple variables and cofactors, such as

disease severity (19). Therefore, preventing inactivity and loss of muscle strength during hospitalization is the best way to prevent DAH.

**Intervention Studies:** The first controlled clinical trials on the effectiveness of interdisciplinary geriatric acute care units designed to prevent or rehabilitate DAH have shown an improvement in functional status at hospital discharge (20, 21). Our interdisciplinary model in the acute care unit also demonstrates a benefit in reducing functional decline and the incidence of delirium during hospitalization (22). Various meta-analyses and systematic reviews demonstrate that interdisciplinary programs aimed at maintaining or improving the functional capacity of the elderly during hospitalization have the potential to improve functional status at discharge, as well as reduce mortality rates, length of stay, and institutionalization rates (23, 24). It seems that interventions that include a follow-up program can maintain positive effects for longer periods of time (24). These studies have limitations: they are very diverse in terms of the type of patients (young or very old elderly), lack a clear description of the type, frequency, and duration of rehabilitation program exercises. Additionally, due to being multidisciplinary programs focused not only on functionality, it is difficult to determine the isolated effect of exercise on functionality. A recent study explores the association of the different components of interdisciplinary models with functional improvement: medication review, early rehabilitation, and individualized treatment appear to be the most effective components (25). There are few studies on the effect of exercise separated from the other components of interdisciplinary models and show contradictory functional results (26, 27, 28).

**AGECAR Study:** Our group has worked on physical activity programs for both institutionalized (29) and hospitalized (30) elderly individuals. In the latter setting, in 2012, we designed a Controlled Clinical Trial of an Exercise Program in Frail Elderly Patients Hospitalized in an Acute Geriatric Unit (30). As a summary (data sent for publication), we included 268 patients, with a mean age of 88 years, 70% of whom met frailty criteria, admitted to an acute geriatric unit. They were randomly assigned, on a monthly basis to avoid contamination, to an intervention group (IG) and a control group (CG). The intervention consisted of an exercise program, in addition to the usual treatment of the control group. The key elements of the daily exercise program were lower limb strengthening through squats and walks of up to 10 minutes in the hallway. The usual treatment of the control group is aimed at preventing functional decline and delirium. The main outcome variable was the change in functional status (measured by scales of basic activities of daily living and ambulation) from admission to hospital discharge and 3 months after discharge. More patients in the IG, compared to the CG, improved from admission to discharge in the number of activities they performed independently, and fewer patients worsened. The proportion of patients who recovered their baseline activities of daily living at 3 months was slightly better in the IG, but the difference was not significant. No beneficial effect was found on the degree of ambulation independence at discharge or at 3 months. This randomized clinical trial provides evidence that an easily applicable exercise program can discreetly improve the ability of a heterogeneous group of elderly patients admitted with acute illness, many of whom are nonagenarians and frail, to independently perform activities of daily living at hospital discharge, but not at 3 months. One of the main limitations of our study was that the median number of days the participants in the IG exercised was only three days. Given the prognostic importance (vital and functional) of disability associated with hospitalization for acute illness, we consider it essential to emphasize exercise programs during hospitalization and health education that improve this disability. Therefore, we intend to introduce modifications to the original program that improve this prognosis and maintain it over time. Basically, the modifications would involve ensuring more days of exercise during admission and including health education sessions so that the patient continues to perform the activities learned in the hospital at home after discharge.

## 2. HYPOTHESIS

A physical training and health education program for elderly patients hospitalized in an acute care unit improves the recovery of disability associated with hospitalization at discharge, and this beneficial effect is maintained at 3 months.

### 98        **3. OBJECTIVES**

#### 99        Primary Objective:

100        To investigate the effect of a physical training program conducted during hospitalization, consisting of  
 101        gait stimulation, lower limb muscle strengthening, and health education, on the physical functional  
 102        capacity of the elderly, as measured by the proportion of patients who recover their baseline Katz index  
 103        (prior to acute illness) at 3 months post-hospitalization.

#### 104        Secondary Objectives:

105        To evaluate the effect of the intervention on recovery at discharge and at 3 months post-hospitalization, in  
 106        terms of functional status measured by other scales of physical function (Barthel Index) and ambulation  
 107        (Functional Ambulation Classification, FAC).

108        To evaluate the effect of the intervention on the change from admission to discharge in functional status  
 109        measured by the Short Physical Performance Battery (SPPB).

110        To evaluate the consistency of differences between the intervention and usual care in subgroups defined  
 111        by age, frailty, presence of delirium, and baseline functional status.

### 112        **4. DESIGN**

113        Randomized clinical trial designed according to the Consolidated Standards of Reporting Trials statement  
 114        (CONSORT) recommendations (Altman DG, Ann Intern Med 2001; 134:663-694). After signing  
 115        informed consent, subjects will be randomly assigned, in blocks of four weeks, to the intervention group  
 116        (IG) or the control group (CG). The IG will undergo the physical training and health education program,  
 117        while the CG will receive standard hospital care. A follow-up phone call will be conducted at three  
 118        months after discharge to assess mortality, number of falls, and functional status. All tests (at admission  
 119        and at discharge) will be conducted in the same hospital unit by the same evaluators not involved in the  
 120        intervention. The study will be conducted following the Ethical Guidelines of the Helsinki Declaration.

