#### 121        SUBJECTS

122        Subjects admitted to the Acute Care Unit of the Geriatrics Department at Gregorio Marañón General  
 123        University Hospital in Madrid. Initial screening will be performed within the first 72 hours of admission.  
 124        Inclusion criteria will be age over 74 years, ability to walk (with or without assistance) before admission,  
 125        ability to communicate, understand, and sign informed consent. Exclusion criteria will be hospital stay  
 126        duration less than 72 hours, presence of any factor that hinders program participation, including terminal  
 127        illness, myocardial infarction or limb fracture in the previous three months, inability to ambulate, severe  
 128        dementia. If a patient who has already been included is readmitted later, they will not be included again.

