#### 129        RANDOMIZATION

130        Randomization will be conducted in blocks of four weeks to avoid overlapping participants in both  
 131        groups. Patients admitted over a four-week period will be assigned to a single group (IG or CG). There  
 132        will be a one-week period without inclusion to discharge patients included in the previous weeks, and  
 133        then another four-week block will begin to assign the next group.

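### The Design section places random assignment after consent, but the admission period sets the arm before screening, so an open-ended exclusion can be applied differently by arm

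*Protocol*

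**What the plan says.** Three parts of section 4 of the protocol bear on this.

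- **Design (opening paragraph).** After "informed consent, subjects will be randomly assigned, in blocks of four weeks, to the intervention group" or the control group. The sequence given is consent, then assignment, and the thing assigned is the subject.
- **Randomization.** "Patients admitted over a four-week period will be assigned to a single group (IG or CG"). A week without recruitment follows, then a new four-week period for the next group. The reason is given too: "Randomization will be conducted in blocks of four weeks to avoid overlapping participants in both" groups.
- **Subjects.** "Initial screening will be performed within the first 72 hours of admission". Entry requires "ability to communicate, understand, and sign informed consent". Among the exclusions is "presence of any factor that hinders program participation, including terminal" illness and several other named conditions. The word before that list makes the named conditions examples, so the criterion itself has no boundary.

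The protocol separates some roles. The Design and Measurement of Variables sections keep those who assess outcomes out of the intervention. Neither says who screens, who takes consent, or whether those people are unaware of the current period's arm.

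**The concern.** If the calendar sets the arm, nothing is left to assign once a patient has signed. A reader of the Design paragraph would take it that enrolment is complete before allocation, which is what protects a randomised comparison from selection at entry. The allocation scheme does not give that protection.

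The open exclusion makes this matter. It asks whether something would hinder taking part in the programme. In an intervention period that is a practical question about a patient who is about to be trained. In a control period it is hypothetical. Someone who knows the current arm can, without breaking any stated rule, exclude a doubtful patient in one period and accept a similar one in another. Willingness to consent is a second filter open to the same influence.

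At stake is the comparability of the arms on the primary outcome, the proportion who regain their pre-admission Katz index at 3 months. Analysis can adjust for factors that were measured, but not for those on which staff judged a patient unsuitable and which nobody recorded.

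**Working it through.** **Order of events.** Under Randomization and Subjects together, a patient's path is:

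1. Admission. The date falls in a period that belongs to one arm, so the arm is set.
2. Screening, up to 72 hours later, including the open exclusion.
3. Consent, which is itself an entry criterion.

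The Design paragraph puts assignment after step 3. Only step 1 is compatible with the Randomization section.

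**Can the arm be known at steps 2 and 3?** The protocol does not say when a period's arm is disclosed, so the first patient of a period could be recruited without knowledge of it. Later patients are harder to protect. The whole unit is on one arm by design, and the intervention is conspicuous: ideally two supervised sessions each weekday, with weighted vests and timed hallway walks (Interventions). No section describes a step that would hide it from recruiting staff.

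**What could it do to the result?** The protocol has no figure for selection, so this is an illustration.

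Inputs from the protocol (Sample Size):
- control recovery 40%, planned intervention recovery 60%, so a planned difference of 20 points;
- 190 patients analysed, so 190/2 = 95 per arm.

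Inputs assumed:
- no true effect, with 40% recovery among all eligible patients;
- a fraction f, with chance of recovery p, screened out in intervention periods only; f and p each 10%–20%.

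Apparent recovery in the intervention arm is q = (0.40 − f·p)/(1 − f). The spurious difference is q − 0.40 = f(0.40 − p)/(1 − f).

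The last column is the chance of a significant result favouring the intervention (two-sided 0.05, 95 per arm, patients treated as independent). It is Φ[(q − 0.40 − 1.96·s0)/s1], where s0 = √(2m(1 − m)/95), m is the mean of 0.40 and q, and s1 = √((0.24 + q(1 − q))/95). With no selection it is 2.5%.

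| f | p | q | Spurious difference | Chance of false significance |
|---|---|---|---|---|
| 10% | 20% | 0.38/0.90 = 42.2% | 2.2 points | 5.0% |
| 10% | 10% | 0.39/0.90 = 43.3% | 3.3 points | 6.7% |
| 20% | 20% | 0.36/0.80 = 45.0% | 5.0 points | 10.3% |
| 20% | 10% | 0.38/0.80 = 47.5% | 7.5 points | 17.9% |

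For the last row: m = 0.4375, s0 = 0.0720, s1 = 0.0718, and (0.075 − 0.1411)/0.0718 = −0.92, which gives 17.9%.

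**Direction.** The sign of f(0.40 − p)/(1 − f) depends on p. The intervention is favoured only if those screened out recover less often than 40%. If they recover more often, the bias goes the other way.

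**The case against.** The best case for the plan has four parts.

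- **The sections do not flatly contradict each other.** The Design sentence itself mentions four-week blocks, and Randomization spells them out. This is fair. The existence of blocks is not in dispute. What remains is that the order (consent, then assignment) and the unit (subjects) are misdescribed.
- **Period allocation is deliberate.** It keeps the two arms from being on the unit together, as the group's previous trial did. This stands, and nothing here argues for replacing it.
- **The criteria are common to both arms.** One list is stated for all subjects, most items are specific, and no text provides for different use by arm. This also stands. The point is that one item is elastic enough to allow it.
- **There is some mitigation.** Katz, frailty, Charlson and APACHE II are collected, and multivariate logistic regression is planned for the primary outcome. That helps with measured differences only.

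Stronger readings are tempting but not supported. A reader might infer that staff know each arm in advance; the protocol does not say when it is disclosed, so knowledge during a running period is likely but inferred. A reader might infer that patients consent knowing their arm; the consent material is not available, so this cannot be judged. A reader might also infer that the result will favour the intervention. The endpoint is return to the patient's own baseline Katz, so a frail patient with a low baseline has fewer activities to regain, and removing such patients need not raise recovery.

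**Conclusion.** The point holds as a weakness in how enrolment is fixed. The Design paragraph does not describe the allocation that the Randomization section sets out: the arm is set by admission period, before screening and consent. With no concealment described for recruiting staff and an open-ended exclusion tied to the programme, selection can depend on the arm, and the planned regression can correct only for what is measured.

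The size is unknown. Under the stated assumptions the spurious difference is 2.2 to 7.5 points, or 11% to 37.5% of the planned 20 points (2.2/20 and 7.5/20), and the chance of a false positive in the intervention's favour rises from 2.5% to between 5.0% and 17.9%. Only the 40%, the 20 points and the 190 come from the protocol; the fraction screened out and its recovery rate are assumptions. This shows a risk that the text leaves open. It is not evidence that selection occurs or that it would run in one direction. The change should be made, and it has to be in place before recruitment to be of full use.

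**What to change.** 1. **Wording.** Correct the Design paragraph to say that four-week periods, not individual patients, are randomised, and that a patient's arm is set by admission date before consent.
2. **Period list.** Generate and hold it off the ward, and reveal each period's arm only when that period starts.
3. **Exclusions.** Replace the open-ended item with a closed list applied identically in every period; its clinical content is for the investigators. Have eligibility recorded before consent by existing staff who do not deliver the training and, where feasible, are not told the arm. The outcome evaluator should not be the one who releases patients to the trainer, because that could unmask the evaluator.
4. **Screening log.** For each period, keep an anonymous count of patients admitted, eligible, excluded with reason, and refusing. Compare the arms on the log and on the baseline data already collected (Katz, frailty, Charlson, APACHE II).

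The cost is a little more record-keeping. The four-week periods and their purpose are untouched. Masking on one ward will be imperfect, so the closed list and the log carry most of the weight: the list narrows discretion, and the log makes differential enrolment visible.

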#### 121        SUBJECTS

122        Subjects admitted to the Acute Care Unit of the Geriatrics Department at Gregorio Marañón General  
 123        University Hospital in Madrid. Initial screening will be performed within the first 72 hours of admission.  
 124        Inclusion criteria will be age over 74 years, ability to walk (with or without assistance) before admission,  
 125        ability to communicate, understand, and sign informed consent. Exclusion criteria will be hospital stay  
 126        duration less than 72 hours, presence of any factor that hinders program participation, including terminal  
 127        illness, myocardial infarction or limb fracture in the previous three months, inability to ambulate, severe  
 128        dementia. If a patient who has already been included is readmitted later, they will not be included again.

#### 129        RANDOMIZATION

130        Randomization will be conducted in blocks of four weeks to avoid overlapping participants in both  
 131        groups. Patients admitted over a four-week period will be assigned to a single group (IG or CG). There  
 132        will be a one-week period without inclusion to discharge patients included in the previous weeks, and  
 133        then another four-week block will begin to assign the next group.

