## MEASUREMENT OF VARIABLES

### Primary Variable:

The proportion of patients who, at 3 months post-hospital discharge, recover the Katz index they had two weeks before admission (baseline) will be measured. The Katz index (Katz S. JAMA 1963; 185:914-919) measures the number of Activities of Daily Living (ADLs) performed independently, including bathing, dressing, toileting, transferring from bed to chair, continence, and feeding. For each ADL, a score of 1 is given if performed independently and 0 if any assistance from another person is required. The range is from 0 to 6.

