## SAMPLE SIZE

Calculated by estimating the proportion of patients who recover their baseline Katz index at 3 months post-hospital discharge. In our AGE CAR study, in the control group, 40% of patients recovered their baseline Katz index at 3 months. With the current intervention, we expect that 60% will recover the Katz index at 3 months. Therefore, with a statistical power ( $1-\beta$ ) of 80% and a significance level ( $\alpha$ ) of 0.05 (two-tailed), we need to analyze a total of 188 patients, rounded to the nearest "10," which is 190 patients. Hospital mortality in our unit is approximately 12%, and assuming a 20% loss to follow-up, we will need to include 252 patients, 126 in the intervention group and 126 in the control group.

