## STATISTICAL ANALYSIS

Groups will be compared using Student's t-test for continuous variables (or its nonparametric equivalent, the Mann-Whitney test), and chi-square test for categorical variables. The effect of training on outcome variables will be analyzed according to the principle of "intention-to-treat." The effect of training on the primary outcome variable, the proportion of patients who recover the Katz index at 3 months, will be analyzed using univariate and multivariate logistic regression. The effect of training on the recovery of other functional status scales will be analyzed similarly. The change in functional status from admission to discharge and 3 months will be classified as improvement if the number of independently performed ADLs increases or deterioration if the number decreases. Differences between groups will be analyzed using the chi-square test for linear trend. The effect of training on these functional scales as continuous variables will be analyzed using repeated measures analysis of variance (ANOVA) with two factors (between-subjects group and within-subjects time). The consistency of differences between the intervention and usual care in subgroups defined by age, frailty, presence of delirium, and baseline functional status will be analyzed using multivariate logistic regression with normal and ordinal models.

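### Allocation is by four-week calendar block, but the sample size and all named analyses treat patients as independent, so the 5% error and 80% power are not assured

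*Protocol*

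**What the plan says.** Section 4 (Design) describes allocation in terms of persons: after "informed consent, subjects will be randomly assigned, in blocks of four weeks, to the intervention group" or the control group. The Randomization section shows what this means in practice: "Patients admitted over a four-week period will be assigned to a single group (IG or CG"). Between blocks there "will be a one-week period without inclusion to discharge patients included in the previous weeks, and" the next block then starts for the next group.

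The primary endpoint is binary: "The proportion of patients who, at 3 months post-hospital discharge, recover the Katz index they had two weeks before admission (baseline) will be measured". The Sample Size section takes its control rate from the earlier AGECAR study ("in the control group, 40% of patients recovered their baseline Katz index at 3 months") and adds a target: "With the current intervention, we expect that 60% will recover the Katz index at 3 months". With 80% power and a two-sided 5% level it concludes "we need to analyze a total of 188 patients", rounded to 190. It then raises the number to include to 252, for hospital mortality and loss to follow-up only.

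Under Statistical Analysis, the primary outcome "will be analyzed using univariate and multivariate logistic regression". The other named methods are the t-test or Mann-Whitney test, chi-square, chi-square for linear trend, and a repeated-measures ANOVA whose two factors are group and time. No block or period term is mentioned anywhere.

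**The concern.** When whole periods are allocated, the trial is cluster-randomised in time. Patients admitted in the same four weeks share a season and whatever else varies on the ward over the calendar. If their outcomes are correlated even slightly, a comparison that counts each patient as a separate unit understates the standard error of the treatment effect. Its confidence intervals are then too narrow and its false-positive rate is above the nominal level. The power statement suffers too: 190 correlated patients carry less information than 190 independent ones, and a test that respects the allocation has only as many independent units as there are blocks.

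The stake is the primary test. A p-value just under 0.05 from the planned logistic regression could not be read at its nominal level, and the stated 80% power would mislead whoever relies on it.

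**Working it through.** **Inputs from the protocol.** Rates 0.40 and 0.60, two-sided alpha 0.05, power 0.80, 188 (rounded to 190) to analyse, 252 to include, 1:1 (Sample Size). Allocation by four-week block (Randomization).

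**Inputs assumed, because the protocol does not give them.** Included patients per block: 10 to 25. This means 252/10 = 25.2 down to 252/25 = 10.1 blocks. Analysed patients per block: m = 10 × 190/252 = 7.54 up to 25 × 190/252 = 18.85. Between-block ICC: 0 to 0.05.

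**Step 1: reproduce the plan's figure.** For independent patients with unpooled variance, the total is

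2 × (1.960 + 0.842)² × (0.4 × 0.6 + 0.6 × 0.4) / 0.20² = 188.4.

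This is the protocol's 188, so the design effect used is 1.

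**Step 2: formulas with block-level allocation.**
- Design effect: DE = 1 + (m − 1) × ICC.
- Actual two-sided error of a test that ignores blocks: 2 × [1 − Φ(1.96/√DE)].
- Power with the correct standard error and a normal reference: Φ(0.20/√(0.48 × DE/95) − 1.96).
- Power with a t reference: non-central t with the same standardised effect, on (blocks − 2) degrees of freedom.

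**Step 3: results with 190 analysed.**

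| Included per block (blocks) | ICC | DE | Error ignoring blocks | Power, normal | Power, t |
|---|---|---|---|---|---|
| 10 (25.2) | 0 | 1.000 | 5.0% | 80.3% | 76.9% |
| 10 (25.2) | 0.001 | 1.007 | 5.1% | 80.1% | 76.6% |
| 10 (25.2) | 0.01 | 1.065 | 5.8% | 77.8% | 74.3% |
| 10 (25.2) | 0.05 | 1.327 | 8.9% | 68.5% | 64.8% |
| 25 (10.1) | 0 | 1.000 | 5.0% | 80.3% | 69.5% |
| 25 (10.1) | 0.001 | 1.018 | 5.2% | 79.6% | 68.8% |
| 25 (10.1) | 0.01 | 1.178 | 7.1% | 73.6% | 62.5% |
| 25 (10.1) | 0.05 | 1.892 | 15.4% | 53.4% | 43.7% |

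Worked example, last row: DE = 1 + 17.85 × 0.05 = 1.892. The error is 2 × [1 − Φ(1.96/1.376)] = 15.4%. The standard error is √(0.48 × 1.892/95) = 0.0978, so power is Φ(0.20/0.0978 − 1.96) = 53.4%.

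**Step 4: separate the two losses.** The rows at ICC 0 show the cost of having few allocated units alone: a block-level t reference gives about 77% to 70% with no correlation at all. The rest of the fall in power comes from the ICC. The error inflation comes only from the ICC.

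**Step 5: check the error formula by simulation.** Beta-binomial blocks were simulated with 10 blocks of 10 analysed patients per arm, 40,000 trials per setting, common recovery rates of 40% and 50%, and a chi-square test ignoring blocks. The test rejected in 6.3% and 6.6% of trials at ICC 0.01, and in 10.8% and 11.5% at ICC 0.05. The formula gives 6.0% and 10.4% for the same settings, so it is slightly optimistic.

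**The case against.** Several points count against pressing this too far.

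First, the size rests on an ICC that the document does not give. The trial runs in one unit with the same evaluators throughout, so the correlation may be very small. At ICC 0.001 the error is 5.1% to 5.2%, and the figures of 15% and 53% need the largest block and the largest ICC together. This stands. The range has to include values near zero, and no single figure can be claimed.

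Second, an unseen statistical analysis plan could add a block term, and the protocol does not list the covariates of its multivariate model. This stands in part. Such a plan could repair the error rate. It could not repair the stated power, because the protocol itself fixes 188 with a design effect of 1. Nor does it change the fact that the protocol names its tests, all of them at patient level, with the ANOVA factors listed in full.

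Third, a reader might infer that block-to-block differences are confounded with arm, or that a shared trainer induces the correlation. The documents do not support either. With several randomly allocated blocks per arm, such differences add noise rather than systematic bias. Nothing says that trainers or staffing change between blocks, and the control arm has no trainer.

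**Conclusion.** The mismatch is certain from the protocol's own text: allocation by calendar block, a sample size for independent patients, and no named analysis that accounts for block. It bears on the validity of the primary test and should be corrected.

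The consequence is that 5% error and 80% power are not assured. The error exceeds 5% for any positive between-block correlation, and a block-level test has less than 80% power because few units are allocated. With 10 to 25 included patients per block, 190 analysed and ICC 0.001 to 0.05, the error is about 5.1% to 15%. Power is about 80% down to 53%, or about 77% down to 44% with a t reference.

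A reader might go further and conclude that the nominal error is definitely breached. The documents do not show that: at ICC 0 the patient-level tests hold their 5% level, and the true ICC is unknown. Confidence is high for the mismatch and limited for its size.

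**What to change.** Describe the trial in Design and Randomization as cluster-randomised by time period, and record the block for each patient. Make one block-aware analysis primary. Options are a block-level t or permutation test, or a logistic mixed model with a random block intercept and small-sample degrees of freedom. If the mixed model is chosen, note that its odds ratio is conditional on block. Handle block the same way in the secondary analyses.

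In Sample Size, state the assumed block size, number of blocks and ICC, and restate power as a range. The Background says that the AGECAR study was also allocated monthly, so its data could supply an ICC.

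The cost is wider confidence intervals and a less favourable stated power; restating it needs no extra patients, visits or data. Recovering 80% power is a separate decision and would not be free. Multiplying 188 by the design effects for ICC 0.001 to 0.05 gives about 190 (188 × 1.007) to 356 (188 × 1.892) patients to analyse, before any allowance for a t reference.
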